### Design and randomization

We will use a type 1 hybrid effectiveness-implementation stepped wedge cluster randomized design to assess both patient-level clinical and practice-level implementation outcomes [25, 26]. The intervention will be implemented sequentially in the 57 participating clinics in three steps over a 4-year period (Fig. 2). All sites will start in the control condition of SOC for weight management. Every year, one sequence of clinics will transition to the intervention condition after which the use of PATHWEIGH will be encouraged for all weight-prioritized visits and corresponding PATHWEIGH implementation strategies will be provided. Clinics were randomly assigned by the study statistician to each sequence using covariate constrained randomization [30] to achieve balance on clinic type (academic, affiliate, non-academic), clinic location (urban/suburban vs. rural), provider type (family medicine (FM), general internal medicine (GIM), or both), annual number of patient visits, and patient insurance status (percentage Medicaid) (Table 1). A stepped wedge extension for this procedure was used to account for the proportion of the study period that each of the sites spend in the control and intervention periods [30]. For additional details about the randomization procedure see Additional file.

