For the primary analysis, although the parameter of interest is weight change at 6 months, weight collected from baseline to approximately 9 months post-baseline for the individual patient will be included in the primary analysis because patients may not have visits with recorded weight within the 6-month time frame. The mixed model will include random intercepts for patient, provider, and clinic, along with fixed effects for time and intervention condition. The time effects are two-fold: (i) calendar time, divided into four 1-year periods and included as a categorical variable to flexibly model its effect on the outcome and account for temporal trends, and (ii) individual patient time, included as a continuous variable (i.e., time from baseline) to accommodate varying visit times determined by each patient’s visit schedule. The intervention condition variable will be a binary indicator that is equal to zero if the patient’s index visit occurs at a clinic when it is in the control condition and becomes equal to 1 when the patient has an index visit at a clinic after it has crossed into the intervention condition. Patient-, provider-, and practice-level covariates will be included in models if deemed to be potential confounders in univariate models. An additional fixed effect for the interaction between patient time and intervention condition will be used to estimate the parameters of primary interest, i.e., the difference in change in outcomes over time between the intervention and control conditions. The primary analysis will test the null hypothesis that the interaction effect coefficient is equal to zero to determine whether there is a significant difference in weight change between the PATHWEIGH and SOC conditions. Using the model, we will report the mean weight change in the control and intervention groups and their difference at 6 months, with corresponding 95% confidence intervals and *p* values.

To examine the secondary binary outcomes of weight maintenance (defined as < 10% weight gain at 12 and 18 months), we will use generalized linear mixed models. Since this analysis will involve a single outcome per patient, the model will only include a random intercept for provider and clinic. The test of intervention effectiveness will be captured by the fixed effect term for the intervention condition.

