The primary analysis is expected to provide a conservative estimate of the treatment effect, and we propose the following secondary analyses to assess the treatment effect in alternative cohorts. We will perform a per-protocol analysis that uses the described models to compare those that received PATHWEIGH to those with a SOC weight-prioritized visit. This analysis will provide a better estimate of the efficacy of the intervention by including only those in the PATHWEIGH condition that were considered to satisfy the criteria for receiving the intervention as assessed by the provider’s use of at least one of a weight prioritized visit “type”, the patient weight management questionnaire, and/or the weight management SmartSet. Additionally, we will perform an analysis using all those that are eligible for PATHWEIGH based on the criteria of age and BMI, regardless of whether they had a weight-prioritized visit. This analysis will allow us to account for the potential selection bias induced by the implementation of PATHWEIGH potentially increasing the number of weight-prioritized visits and thus increasing the enrollment of patients in the intervention period that differ systematically from those in the control period.

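### Read as written, the covariates in the primary model adjust weight level and not the weight-change contrast that is tested

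*Protocol article*

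**What the plan says.** The Aim 1 Analysis section sets out the primary model in some detail.

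- **Outcome data:** "weight collected from baseline to approximately 9 months post-baseline for the individual patient will be included in the primary analysis". The baseline weight is thus one of the outcomes.
- **Structure:** "The mixed model will include random intercepts for patient, provider, and clinic, along with fixed effects for time and intervention condition". No random slopes are mentioned. Time enters as calendar year (categorical) and as patient time (continuous).
- **Interaction:** "An additional fixed effect for the interaction between patient time and intervention condition will be used to estimate the parameters of primary interest".
- **Test:** "The primary analysis will test the null hypothesis that the interaction effect coefficient is equal to zero".
- **Covariates:** "Patient-, provider-, and practice-level covariates will be included in models if deemed to be potential confounders in univariate models".

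No covariate is named in that rule, and none is exempt from the screen. This includes the factors used to constrain the randomisation, which was done "to achieve balance on clinic type (academic, affiliate, non-academic), clinic location (urban/suburban vs. rural), provider type", annual visits and percentage Medicaid (Design and randomization). Baseline BMI is named under Aim 2 as a possible moderator, to be examined through treatment by moderator terms outside the primary test.

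On case mix, the article allows that PATHWEIGH may raise the number of weight-prioritized visits, thereby "increasing the enrollment of patients in the intervention period that differ systematically from those in the control period". It calls this potential selection bias and plans a secondary analysis of everyone eligible by age and BMI, with or without such a visit.

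**The concern.** The tested parameter is a difference in slopes. A covariate that is fixed over time and entered as a main effect explains why some patients weigh more than others. It does not explain why some lose more than others. The patient intercept and the baseline weight already absorb differences in level, so the main effect has almost nothing left to do for the slope contrast.

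This matters because only clinics are randomised. Patients enter through a weight-prioritized visit, which the intervention itself encourages. Baseline BMI is a credible driver of change in kilograms. The Clinician workflow section ties treatment options to BMI thresholds, and the same percentage loss is more kilograms in a heavier patient. If the BMI mix differs between conditions, the primary estimate carries that difference whether or not BMI passes the screen. Depending on its direction, the imbalance could create an apparent benefit or hide a real one.

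**Working it through.** **1. The plan's own figure.** Inputs from Sample size, Table 1 and the Aim 1 Analysis: 57 clinics (20/18/19), four yearly periods, 30 patients per clinic-year, two-sided alpha 0.05, 80% power, SD 10.7 kg. The Hussey-Hughes variance for a cross-sectional stepped wedge, with total variance 1, is

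Var = I·s²(s² + Tτ²) / [(IU − W)s² + (U² + ITU − TW − IV)τ²],

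with I = 57, T = 4, s² = (1 − ICC)/30 and τ² = ICC. From the design, U = 115, W = 5093 and V = 271, so IU − W = 1462 and the second bracket is 3626.

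- ICC 0.02: SE = 0.0418; detectable effect 2.80 × 0.0418 = 0.117 (stated 0.118).
- ICC 0.05: SE = 0.0429; detectable effect 2.80 × 0.0429 = 0.120 (stated 0.121).

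In kilograms, 0.118 × 10.7 = 1.26 and 0.121 × 10.7 = 1.29, as stated. The sample size is sound and is not in question. The SE implied by 1.26 kg is 1.26/2.80 = 0.45 kg.

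**2. Why a main effect does not help.** Let the true weight of patient i at time t contain βx + γxt, where x is a baseline covariate. Leaving out γxt puts a bias of about 6γ × (mean x under PATHWEIGH − mean x under standard of care) into the 6-month contrast. Adding βx changes this little. With a large between-patient variance, the slope is estimated almost wholly from changes within patients, and βx cancels from those changes. Adding γxt removes the bias.

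**3. Check by simulation, true treatment effect zero.** The document gives neither the imbalance nor the effect of BMI on weight change, so both are assumed.

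*BMI classes.* Assumed 6-month losses are 1, 3 and 8 kg for BMI below 30, 30 to 39.9, and 40 or more. The assumed mix is 30/50/20% under standard of care and 20/50/30% under PATHWEIGH. Expected losses are 0.3 + 1.5 + 1.6 = 3.4 kg and 0.2 + 1.5 + 2.4 = 4.1 kg, a spurious difference of 0.70 kg. Over 300 simulated trials of 6840 patients with a patient intercept, the estimated difference was −0.70 kg without covariates, −0.70 kg with BMI-class main effects and 0.00 kg with BMI class by patient time (Monte Carlo SE 0.017). A repeat with clinic effects gave −0.70, −0.70 and 0.01 kg.

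*Continuous BMI.* Patient intercept, clinic effects fitted, four weights over 0 to 9 months, no provider level, Monte Carlo SE about 0.02 kg:

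| Imbalance (SD) | 6-month change per SD (kg) | No covariate | Main effect | Main effect and × time |
|---|---|---|---|---|
| 0 | −2 | −0.02 | −0.03 | −0.01 |
| 0.1 | −1 | −0.08 | −0.12 | 0.01 |
| 0.2 | −1 | −0.20 | −0.21 | 0.02 |
| 0.2 | −2 | −0.40 | −0.36 | 0.02 |
| 0.3 | −2 | −0.62 | −0.59 | −0.02 |

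**4. Consequence for the test.** With bias b and SE 0.45 kg, the false-positive rate is 1 − Φ(1.96 − b/0.45) + Φ(−1.96 − b/0.45).

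| Bias (kg) | b/0.45 | False-positive rate | Share of 1.26 kg |
|---|---|---|---|
| 0.12 | 0.27 | about 6% | 10% |
| 0.59 | 1.31 | about 26% | 47% |
| 0.70 | 1.56 | about 34% | 56% |

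**The case against.** The strongest reply is that the article never says main effects only. It says that covariates will be included, and it may list one interaction simply because that is the tested one. Functional form is often left to an analysis plan, which is not shown here and could add covariate by time terms. This stands as a limit on the wording: main effects are an inference from a model that is otherwise spelled out. It does not remove the point, because the article does fix a covariate rule, and that rule as written does not reach the tested coefficient.

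The second reply is that the selection risk is already handled. The all-eligible analysis is aimed at this mechanism, and it also covers unmeasured selection such as motivation, which BMI terms cannot. That is a real safeguard. It is secondary, however, and concerns a different population, so it does not repair the primary estimate.

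A reader might also infer four stronger claims that the document does not support:

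- **That the article expects the two patient groups to differ.** It speaks only of potential bias.
- **That the primary estimate is off by 0.70 kg with a 34% false-positive rate.** That is one assumed scenario, at the unfavourable end of those tried.
- **That the five randomisation factors bias the result.** No such bias has been shown. Every clinic starts in standard of care and crosses over, and the constrained randomisation allowed for time spent in each condition.
- **That the screen would drop those factors.** The article does not say whether the univariate models look at weight level, weight change or condition.

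**Conclusion.** The concern holds for the primary model as written. Screened covariates, read as main effects, leave the patient time by condition coefficient about as exposed to baseline confounding as using no covariates at all. This structural result does not depend on the assumed BMI figures.

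The size does depend on them. It is nil if no covariate that predicts weight change is imbalanced, and about 0.1 to 0.7 kg over the assumed imbalances and slope effects. The matching false-positive rates of about 6% to 34% also rest on the SE of 0.45 kg, which is derived from the sample-size section and not from the repeated-measures model. The plan should be changed, since the gap sits in the primary analysis and closing it costs little.

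**What to change.** In the Aim 1 Analysis section, replace the univariate screen with a prespecified set measured at or before the index visit: baseline BMI, age, sex and insurance. Enter each as a main effect and in interaction with patient time. Estimate the 6-month mean changes and their difference from that model, standardised over the observed covariate distribution. The timing restriction matters because the Aim 1 covariate data include the treatment used, which Aim 2 treats as a mediator.

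Include the five constrained-randomisation factors without screening, mainly for precision and to match the design. By the same reasoning, they need the patient-time interaction to bear on the tested contrast. The gain is small: if they explain 30% to 60% of the clinic variance at ICC 0.05, power rises from 80% to about 81% to 83%. Keep the model without these terms as a sensitivity analysis.

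The cost is a longer model statement and some parameters. With insurance in four categories (assumed), the patient covariates need 1 + 1 + 1 + 3 = 6 terms and the clinic factors 2 + 1 + 2 + 1 + 1 = 7. That makes 13 main effects and 13 interactions against 6840 patients, and a few degrees of freedom among 57 clinics. No new data are needed: the clinic factors are known, and the patient variables already come from the medical record.

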**Fig. 3 Fig3:**
[figure not shown]
SPIRIT diagram

Retrospective data will be collected on all patient encounters at the 57 primary care clinics at the specified times described above. Specifically, how many patient visits occurred at each clinic, how many discrete patients were seen at each clinic, how many patients were ≥18 years old with a BMI ≥ 25 kg/m^2^, and how many patients who were ≥18 years old with a BMI ≥25 kg/m^2^ had a weight-prioritized visit (either in person or by telehealth). These data will be illustrated in an Expanded CONSORT diagram [31]. Data will be stored on a secure data server with access provided to the study statisticians. The statisticians will not be blinded to the assignment of the interventions.

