## Evaluation

### Aim 1: Compare the effectiveness of PATHWEIGH versus standard of care (SOC) on weight loss and weight loss maintenance.

#### Outcomes and Measures

The primary outcome is patient weight between baseline and 6 months in kilograms (kg) as measured by a standard scale. The secondary outcome of weight loss maintenance will be defined at 12 and 18 months as a binary outcome of weight increase ≤ 10% from the patient’s 6-month weight. Weight outcomes will be extracted from the EMR. The primary independent variable will be the intervention status, which will be determined based on visit date and practice sequence. Additional covariate data will be collected from the EMR on potential confounders at the level of patient, provider, and practice. Patient-level data will include demographic information, health metrics, behaviors and goals, and treatment strategy employed. Provider-level data will include demographic information, years practicing, and percent time practicing. Clinic-level data will include site type/discipline, location, and size. Outcomes, measures, and timing of data collection are described in Table 3.

**Table 3 Tab3:** Summary of outcomes, measures, data sources, and timing of collection for PATHWEIGH study

Construct	Metric/measure	Method of collection	Timing

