### Aim 2: Identify patient, provider, and clinic-level predictors that are associated with weight loss and weight loss maintenance

#### Outcomes and measures

Patient-level predictors will be captured from the EMR for each visit. Potential patient-level moderators will include age, sex, race/ethnicity, insurance status, baseline BMI, baseline use of medication that may contribute to weight gain, and score > 9 on Patient Health Questionnaire-8 or -9 (PHQ8, PHQ9), or Generalized Anxiety Disorder-7 (GAD7). Patient-level mediators will include treatment prescribed, in particular prescription of anti-obesity medication and performance of an endoscopic or surgical procedure with bariatrics. Provider-level predictors that can be obtained from EMR include provider age, sex, years in practice, and percent time performing clinical duties. Practice-level predictors include patient and provider number and demographics for each, as well as payor mix.

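### The univariate confounder screen for the Aim 1 models can admit treatment strategy, which the plan itself treats as a mediator: a direct problem for the 12- and 18-month models, a conditional one for the primary model

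*Protocol article*

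**What the plan says.** Under Aim 1, Outcomes and Measures, the protocol article introduces the covariates: "Additional covariate data will be collected from the EMR on potential confounders at the level of patient, provider, and practice". It then lists them by level, and for patients it says: "Patient-level data will include demographic information, health metrics, behaviors and goals, and treatment strategy employed".

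The Aim 1 Analysis section gives the rule for using them: "Patient-, provider-, and practice-level covariates will be included in models if deemed to be potential confounders in univariate models". It sets no limit to variables measured at or before the index visit, and it does not exclude mediators.

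The same section calls the primary analysis intention-to-treat, by the clinic's condition at the index visit. The primary test is the interaction of patient time with condition. For the 12- and 18-month binary outcomes the test is the main effect of condition.

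Under Aim 2, Outcomes and measures, treatment has another role: "Patient-level mediators will include treatment prescribed, in particular prescription of anti-obesity medication and performance of an endoscopic or surgical procedure with bariatrics". Table 2 says that the PATHWEIGH SmartSet suggests weight-loss approaches, so treatment choice is one route by which the intervention is meant to act.

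**The concern.** An intention-to-treat comparison by clinic condition targets the total effect of PATHWEIGH, including whatever it achieves by changing treatment. Treatment strategy follows the index visit and is part of that pathway. If it enters an Aim 1 model in a form that bears on the tested coefficient, that coefficient becomes a direct effect. This is the structure of the Aim 2 outcomes model, which estimates the mediator's effect with condition also in the model.

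A univariate screen gives no protection. A working mediator is associated with both condition and outcome, which is also how a confounder looks. The more PATHWEIGH works through treatment, the more likely the variable is to pass.

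At stake are the secondary maintenance tests and, depending on how the covariate is coded, the primary estimate. The per-protocol analysis reuses the same models and inherits the rule.

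**Working it through.** **1. The plan's own figure.** Inputs from Sample size: 57 clinics, 30 patients per clinic-year, 4 years, two-sided alpha 0.05, 80% power, ICC 0.02 to 0.05, SD 10.7 kg. The Hussey-Hughes cross-sectional variance (three sequences of 19, four periods) gives detectable standardized effects of 0.1174 and 0.1204, against 0.118 and 0.121 stated. In kilograms, 0.118 × 10.7 = 1.26 and 0.121 × 10.7 = 1.29, as stated. The power statement reproduces. The implied standard error is 1.26 / 2.80 = 0.45 kg.

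**2. Primary model: the form of entry decides.** Assumed inputs (the documents give none): treatment use of 10% under standard of care and 30% under PATHWEIGH, and four weights at t = 0, 0.5, 1 and 1.5 in units of 6 months. If treatment is worth 6.3 kg at 6 months and there is no direct effect, the total is 0.20 × 6.3 = 1.26 kg.

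- *Time-constant main effect.* The covariate does not vary within a patient, so it shifts weight level and does not compete with the slope. The estimate stays at 1.26 kg. Simulations agree: −1.01 kg with and without the covariate in one scenario (true total −1.0), −1.23 kg both ways in another (true total −1.25).
- *By-visit flag (0 at the index visit, 1 after).* Within-patient deviations are (−0.75, −0.25, 0.25, 0.75) for t and (−0.75, 0.25, 0.25, 0.25) for the flag. The sums are S_tt = 1.25, S_DD = 0.75 and S_tD = 0.75, so the flag's slope on t is 0.75 / 1.25 = 0.6. With use p in each condition and about equal shares of patients, the flag takes Σ0.75p(1−p) / Σ(0.75p − 0.45p²) = 0.225 / 0.255 = 0.88 of the treatment effect. The mediated part retained in the tested coefficient is 1 − 0.6 × 0.88 = 0.47, or about 0.59 kg. Simulation of these inputs gave 0.65 kg. With 5% and 25% use and 5 kg, it fell from −1.01 to −0.48 kg.
- *Treatment with its time interaction.* The mediated slope is fully absorbed. Simulations gave 0.00 and −0.03 kg.

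**3. Range over the mediated share.**

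| Entry of treatment | All of 1.26 kg mediated | Half direct (0.63 kg) |
|---|---|---|
| Time-constant main effect | 1.26 | 1.26 |
| By visit | about 0.6 | about 0.92 |
| With time interaction | about 0 | about 0.62 |

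The half-direct column agrees with the algebra: 0.63 + 0.63 × 0.47 = 0.93, and 0.63 + 0 = 0.63. With the standard error held at 0.45 kg, power is Φ(2.80 × share − 1.96). It is about 29% at half the planned effect and 56% at three quarters. These powers belong to the conservative sample of 6840; a larger sample would soften the power loss but not the bias.

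**4. Secondary binary models.** There is one outcome per patient, and the tested term is the condition main effect. If condition affects maintenance only through treatment, the outcome probability given treatment is the same in both conditions, so the adjusted condition effect is zero whatever the total effect. With a partial direct effect, the direct part remains. No special coding is needed. No size can be given, because the documents state neither maintenance rates nor a mediated share. The direction is a tendency, since conditioning on a post-index choice can also bring in confounding between treatment and weight.

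**The case against.** The strongest objection concerns the primary test. The Analysis section says only that covariates are included, and the one interaction with patient time that it names is that of condition. Read plainly, treatment strategy would be a main effect, and the primary estimate would not move. By-visit entry finds support only in "Patient-level predictors will be captured from the EMR for each visit", which describes Aim 2 predictors, and a treatment-by-time term appears nowhere in the plan. The inputs that produce a near-total loss also assume full mediation. All of this stands.

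A reader might therefore infer that the primary effect will be adjusted away. The documents do not support that. They permit it under particular codings and do not commit to them.

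It can also be said that the word deemed leaves room for judgement, that the authors plainly know treatment is a mediator, and that a screening criterion may be set in an analysis plan not shown. That is fair against treating the missing criterion, or the unblinded statisticians ("The statisticians will not be blinded to the assignment of the interventions"), as errors in themselves. It does not answer the main point: the article states a rule and names a mediator among its candidates.

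A reader might also infer that failing to commit the factors that constrained the randomisation harms the primary comparison. No such effect is shown. Every clinic crosses over, clinic has a random intercept, and a clinic-level prognostic covariate added as a main effect left the estimate at −1.26 kg.

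**Conclusion.** The concern holds as a defect in a stated rule. Aim 1 can adjust for a variable that Aim 2 calls a mediator, against the declared intention-to-treat effect. The direct exposure is in the 12- and 18-month models, where plain adjustment conditions on the mediator and would tend to pull the tested effect toward the null. In the primary model the exposure is conditional: essentially none with a time-constant main effect; about half of the mediated part lost with by-visit entry; nearly all of it with a time interaction. The kilogram figures rest on assumed prescribing rates, treatment effect, visit times and mediated share, none of which the documents give. It should be fixed, but it does not show that the primary analysis as written is biased.

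**What to change.** Replace the screening sentence with a prespecified list of covariates fixed at or before the index visit, for example age, sex, race/ethnicity, insurance, comorbidity and baseline use of weight-affecting medication. In the primary model, add their interactions with patient time where they are meant to adjust weight change, since a main effect adjusts only weight level. State that treatment strategy, and any other variable decided at or after the index visit, is excluded from all Aim 1 models, and keep treatment strategy for the Aim 2 mediation analysis. Adding the randomisation-constraint factors is reasonable but optional for this point.

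The cost is wording. The stated detectable differences do not change. The list should be checked against the fields that can be extracted, because the eligibility section reports that some planned fields could not be obtained.

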## Aims and hypotheses

The specific aims of the current research are to:
Compare the effectiveness of PATHWEIGH versus standard of care (SOC) on weight loss and weight loss maintenance.Identify patient, provider, and clinic-level predictors that are associated with weight loss and weight loss maintenance.Describe factors associated with practice adoption, implementation, and maintenance of PATHWEIGH.

We hypothesize that PATHWEIGH will lead to greater weight loss at 6 months (primary) and greater weight loss maintenance at 12 and 18 months (secondary) compared to SOC [Hypothesis I]. Key patient, clinician, and clinic characteristics will mediate and moderate patient weight loss and weight loss maintenance [Hypothesis II]. Effective implementation will be vital to anticipated implementation and clinical outcomes [Hypothesis III].

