### Sample size

A conservative sample size estimate is 6840 total patients (120 patients per clinic from 57 clinics) that assume a minimum of 30 eligible patients per clinic per year based on the smallest clinic. We present the power calculations assuming an intraclass correlation coefficient (ICC) between 0.02 and 0.05. With this design, we will have 80% power (alpha=0.05, two-sided) to detect a standardized effect size of 0.118 (ICC=0.02) to 0.121 (ICC=0.05). For our primary effectiveness outcomes, we estimate a standard deviation (SD) of 10.1 percentage points for percentage change in weight using our pilot study, and a similar SD estimate of 10.7 for absolute (kg) change in weight. Thus, with 80% power we can detect a mean difference in weight change of 1.19 (ICC=0.02) to 1.22 (ICC=0.05) percentage points between the control and intervention conditions, and a mean difference in absolute weight change of 1.26 kg (ICC=0.02) to 1.29 kg (ICC=0.05).

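### The 12- and 18-month maintenance hypothesis is tested only on a yes/no cut of a continuously recorded weight, which on the pilot SD keeps about half of the information

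*Protocol article*

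**What the plan says.** Hypothesis I (Aims and hypotheses) includes "greater weight loss maintenance at 12 and 18 months (secondary) compared to SOC [Hypothesis I"]. The Aim 1 Outcomes and Measures section makes this a dichotomy, "defined at 12 and 18 months as a binary outcome of weight increase ≤ 10% from the patient’s 6-month weight". The Aim 1 Analysis section then sets the method: "To examine the secondary binary outcomes of weight maintenance (defined as < 10% weight gain at 12 and 18 months), we will use generalized linear" models with random intercepts for provider and clinic. It goes on to state: "The test of intervention effectiveness will be captured by the fixed effect term for the intervention condition".

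The primary outcome is weight in kg, analysed on its full scale with weights up to about 9 months. No continuous model is described for 12 or 18 months, and the per-protocol analysis reuses the same models. The abstract speaks of differences in weight loss and maintenance at 6, 12 and 18 months but names no further test.

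The Sample size section covers the primary effectiveness outcomes only: "we will have 80% power (alpha=0.05, two-sided) to detect a standardized effect size of 0.118 (ICC=0.02) to 0.121 (ICC=0.05"), and "we estimate a standard deviation (SD) of 10.1 percentage points for percentage change in weight using our pilot study". It gives no SD, maintenance rate, target effect or power for the later outcome.

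**The concern.** The same scale weight is used whole at 6 months and cut in two afterwards. On the only SD in the article, a gain of 10% lies about one SD above a mean change near zero. Most patients in either condition would count as maintainers, and the test would see only movement across that one line. A patient who regains 1% and one who regains 9% count the same.

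Half of Hypothesis I depends on this test. A non-significant result could be reported as no benefit for maintenance when it partly reflects the scale chosen.

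**Working it through.** **Inputs from the article.** Sequences of 20, 18 and 19 clinics (Table 1); four one-year periods; 30 patients per clinic-year; ICC 0.02 to 0.05; two-sided alpha 0.05; SD 10.1 points; cut at +10%.

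**Assumptions not in the article.** Percentage change after month 6 is normal with SD 10.1; mean regain m under standard care is 0 to 2%; the benchmark effect is the one that a continuous test on the same design would detect with 80% power.

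**1. Reproduce the plan's figure.** Generalized least squares on clinic-period means, with categorical period and a random clinic intercept, gives a standard error for the intervention effect of 0.0418 SD (ICC 0.02) and 0.0429 SD (ICC 0.05). Multiplying by 1.960 + 0.842 = 2.802 gives detectable effects of 0.117 and 0.120, against the stated 0.118 and 0.121. On the percentage scale, 0.118 × 10.1 = 1.19 and 0.121 × 10.1 = 1.22, as stated.

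**2. Place the cut.** c = (10 − m)/10.1.
- m = 0: c = 0.990. The share gaining more than 10% falls from 16.1% to 13.4% under a 0.117 SD shift.
- m = 2: c = 0.792. The share falls from 21.4% to 18.2%.

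**3. Information kept.** Relative efficiency = φ(c)² / [p(1 − p)], with p the share above the cut.
- m = 0: 0.2444² / (0.1611 × 0.8389) = 0.442.
- m = 2: 0.2915² / (0.2142 × 0.7858) = 0.505.

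**4. Power.** Φ(2.802 × √efficiency − 1.960).
- m = 0: 2.802 × 0.665 − 1.960 = −0.097, so 46%.
- m = 2: 2.802 × 0.711 − 1.960 = 0.031, so 51%.

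Putting the binary outcome through the step 1 design, with the ICC converted to the binary scale (for example 0.02 becomes 0.0089 at m = 0), gives 46 to 47% at m = 0 and 51 to 53% at m = 2. The efficiencies that these powers imply run from ((1.960 − 0.105)/2.802)² = 0.44 to ((1.960 + 0.063)/2.802)² = 0.52. At m = 0, restoring 80% would take about 1/0.442 = 2.26 times the sample.

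**5. Vary the assumptions.**

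| Scenario | Binary | Continuous |
|---|---|---|
| SD 10.1, m from −2 to +5%, 30 per clinic-year | 40–57% | 80% |
| SD 10.1, m 0–2%, 60 per clinic-year (assumed) | 72–79% | 97% |
| SD 10.1, m 0–2%, 100 per clinic-year (assumed) | 90–94% | over 99% |
| SD 5–7, m 0–2%, effect fixed at 1.19 points, 30 per clinic-year | 50–79% | 98% or more |
| SD 7, m 0–2%, effect fixed at 0.117–0.120 SD | 33–43% | 80% |
| SD 5, m 0–2%, effect fixed at 0.117–0.120 SD | 18–29% | 80% |

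In the last two rows the effect in points shrinks with the SD: at ICC 0.02 it is 0.117 × 7 = 0.82 and 0.117 × 5 = 0.59 points. The continuous test has more power in every row.

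**The case against.** **No planned power is lost.** A reader might infer that the trial promised 80% power for maintenance and gives it up. The article does not support that: the 80% belongs to the primary outcomes, and here it is only a benchmark. This stands.

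**Power need not be as low as half.** A reader might also infer that power is 46 to 53% or lower. The lower figures need the effect in points to shrink along with the SD. At a fixed 1.19 points, a smaller SD mostly raises binary power. The 6840 patients are also a declared floor based on the smallest clinic, and the expected number of eligible patients per clinic is not given. Missing later weights would pull the other way and cannot be sized either. This stands against any unconditional figure, but not against the comparison between the two scales.

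**A mean difference answers a different question.** Maintenance is a status of not regaining much. If PATHWEIGH produces more loss by month 6, its patients have more to regain, so mean change from month 6 could count against it. It therefore cannot be said that the weights would show a benefit that the cut hides. This stands. It argues for adding a continuous analysis with a carefully chosen reference, not for discarding the maintenance outcome.

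**The analysis plan is not shown.** It may give the reason for the 10% limit or add supportive analyses, so the absence of a rationale is not held against the article. But the article itself names the endpoint and the single test of effectiveness, and that choice can be judged as written.

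**Conclusion.** The point holds in conditional form. The secondary hypothesis at 12 and 18 months is tested only on a dichotomy of a continuously recorded weight. With SD 10.1, a normal change and mean regain of 0 to 2%, the cut keeps about 44 to 52% of the information. At 30 patients per clinic-year, power is about 46 to 53% where a continuous test would have 80%. The absolute figures move with the sample size, SD, mean regain and effect after month 6, none of which the article fixes for this outcome; the advantage of the continuous test persisted in every scenario tried. The primary analysis is unaffected. The change is worth making because the hypothesis is a named one and the remedy is cheap.

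**What to change.** In the Aim 1 Outcomes and Measures and Analysis sections:

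- Add continuous percentage (or kg) weight change at 12 and 18 months as a tested secondary analysis. Use a linear mixed model with the same intervention term, calendar-period effects, and provider and clinic random intercepts. Report the mean difference with its 95% CI at each time.
- Name the reference weight. Change from baseline avoids conditioning on a 6-month weight that the intervention may already have altered; change from month 6 can be shown beside it.
- Keep the proportion gaining no more than 10% as the maintenance summary, with its CI.
- Reconcile the definition. Outcomes and Measures allows a gain of exactly 10% and names the 6-month weight; the Analysis section uses a strict inequality and names no reference. This does not change the figures above.

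The cost is wording only, since the weights are already to be extracted. The downside is one more secondary estimate per time point, which is less readable than a proportion and more sensitive to extreme weights.
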